## Methods

### Study design

DocosaHexaenoic Acid supplementation during pregnancy and lactation on Neurodevelopment of the offspring in India (DHANI) is a double-blinded, randomized, placebo controlled trial being conducted in India. Study participants are healthy pregnant women and their offsprings.

DHANI will assess the impact of 400 mg of pre- and post-natal DHA supplementation (from ≤20 weeks of gestation to 6 months postpartum) on infant neurodevelopment at 6 and 12 months as measured by the Development Assessment Scale for Indian Infants (DASII). Secondary objectives of this trial include an assessment of the impact of maternal DHA supplementation on: gestational age, new born anthropometry (birth weight, length and head circumference) and APGAR score; infant anthropometry (birth weight, length and head circumference) at birth, 1 month, 6 months and 12 months; number of unfavorable pregnancy outcomes (still births, low birth weight babies, preterm babies); morbidity patterns through 12 months in the two groups. The first mother was enrolled on 6 Jan 2016 and the last on 31st Aug 2017. The data being collected under the trial for mother-infant dyads at each time point has been presented in Table 1.

**Table 1 Tab1:** Data being collected under DHANI trial

Domain	Measure	Data obtained on woman						Data obtained on child		
		Pregnancy		Delivery	Post partum/ lactation			Birth	6 months	12 months
		Enrolment at < =20 weeks	Each month until Delivery	Delivery	2-3rd Day Post partum	1 month Post partum	6 month post partum			
Socio-economic and demographic profile	Demographics	X								
	family details	X								
	Income	X								
	Education	X								
	Occupation	X								
Medical and Obstetric History	Clinical Investigation	X	X	X	X		X	X	X	X
	Obstetric History	X								
	Complications	X	X	X	X	X	X	X	X	X
	Adverse events	X	X	X	X	X	X	X	X	X
	Eligibility	X								
Blood	Fatty acid composition	X		X			X	X	X	X
Breast milk (30%)	Fatty acid composition				X	X	X			
Body Size & composition	Anthropometry (weight, length, mid upper arm circumference, head circumference of offspring)	X	X	X	X	X	X	X	X	X
Behavioral Factors	Dietary Intake	X							X	X
	Physical activity	X					X			
	Prenatal Care	X	X							
	Substance use	X								
Child development	APGAR							X		
	Developmental Quotient								X	X
	Morbidity	X	X	X	X	X	X	X	X	X

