### Effect size, power and sample size

The primary outcome variables are infant motor and mental development quotient at 12 months of age. The smallest effect sizes of interest were 0.25 S.D. for motor and mental development at 12 months of age [42]. Using a two-tailed test and a significance level of α = 0.05, a final sample of 338 infants per group (676 mother-child dyads) was required at the end of the study (12 months postpartum) to provide 90% power. A total of 957 mothers have been recruited in the present study, allowing for potential attrition due to serious adverse events, withdrawal, and migration out of the study area. Breast-milk samples are being collected within 3–4 days after delivery and at 1 month and 6 months postpartum from a 30% convenience sub-sample - 150 mother-infant pairs per group, which will have 95% power to detect effect sizes of 0.5 S.D. in DHA levels.

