### Statistical analyses

All the analyses will be performed on the principle of ‘intention to treat’ unless otherwise specified (i.e., we will compare patients in the groups to which they were originally randomly assigned). Statistical analyses will be performed using STATA Version 14.0. We will summarize maternal and household characteristics in the two groups and assess the effectiveness of randomization by comparing these between the groups. Continuous, normally distributed variables will be summarized as means and standard deviations, while skewed variables will be summarized as medians and inter-quartile ranges. Categorical/binary variables will be summarized using proportions. Comparisons on baseline characteristics will also be made between the final study sample and those who were lost to follow up.

For the primary outcome, we will test the unadjusted difference in the mean DASII score at 6 months and 12 months between the two treatment groups using a two-sample t-test. For adjusted analyses, we will consider the DASII score as a continuous variable and use a multiple linear regression model, adjusting for treatment, sex of the child, maternal age, maternal education, socio economic status, birth-weight and other factors which we find out to be significant at baseline comparison. We will adjust for the 6 month DASII score in the model examining the difference in score at 12 months between the treatment groups using Generalized Estimating Equation (GEE) analyses to account for correlation between the 6 month and 12 month DASII score.

The DASII score will also be analysed as a binary variable. DASII score ≤ 70 will be used to defined developmental delay. The unadjusted and adjusted relative risk in the proportion of DASII score (≤70) at 12 months between DHA and placebo groups will be calculated using a log-binomial regression. In case of convergence issues with the log-binomial model, logistic regressions will be used to conduct the adjusted analyses and adjusted odds ratios will be reported instead of adjusted relative risks.

The differences in weight, length, head circumference, still birth, Apgar score at 1 min & 5 min of the infants at birth will be tested using t-test. Adjusted analyses will be performed using multiple linear regression.

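### The adjusted 12-month DASII model is worded to condition on the 6-month DASII score, a post-randomisation outcome, which would attenuate the adjusted effect; the stated GEE purpose implies a different model

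*Protocol article*

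**What the plan says.** The Effect size, power and sample size section places the primary outcome at one age: "The primary outcome variables are infant motor and mental development quotient at 12 months of age". The Primary outcome section likewise defines it as a mean difference at 12 months.

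The Statistical analyses section gives three steps for it. First, an unadjusted two-sample t-test at 6 and at 12 months. Second, a multiple linear regression with treatment, sex, several maternal and household factors and birth weight. Third, this sentence: "We will adjust for the 6 month DASII score in the model examining the difference in score at 12 months between the treatment groups", which continues "using Generalized Estimating Equation (GEE) analyses to account for correlation between the 6 month and 12 month DASII score".

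Other sections fix what the 6-month score is. Exposure has women take capsules from at most 20 weeks of gestation until 6 months postpartum. Data collection has the DASII given at 6 and again at 12 months. Study design names neurodevelopment at both ages as what the trial will assess.

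**The concern.** Adjusting an outcome for an earlier value of the same scale is sound when the earlier value precedes randomisation. Here it cannot: a DASII score at 6 months of age comes after the whole course of supplementation and can be changed by it. Conditioning on it replaces the question of how much DHA changes the 12-month score with the question of how much the arms differ at 12 months among infants with the same 6-month score. That is close to asking what is added after the capsules stop. The article states no such aim, and its Discussion describes the total effect.

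The sentence also pulls in two directions. As a covariate, the 6-month score leaves one outcome per infant, so GEE has no within-child correlation to handle. As an outcome, it gives GEE a purpose, but then it is not adjusted for. The two models estimate different treatment effects.

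At stake is the adjusted result for the primary outcome. If benefit appears by 6 months and persists, which is a natural form of the trial's hypothesis, the covariate version would report a smaller effect than the t-test beside it. That could be misread as a result that fails to survive adjustment.

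**Working it through.** **Inputs from the protocol** (Effect size, power and sample size): "The smallest effect sizes of interest were 0.25 S.D. for motor and mental development at 12 months of age"; "Using a two-tailed test and a significance level of α = 0.05"; "to provide 90% power"; "a final sample of 338 infants per group (676 mother-child dyads) was required".

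**Assumed, because the protocol gives neither:** the within-arm correlation r between the 6- and 12-month scores (0.3 to 0.7), and the 6-month effect d6 (0, 0.125 or 0.25 SD). SDs are taken as equal at the two ages.

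**Step 1: the plan's own figure.** n per group = 2 × (1.960 + 1.282)² / 0.25² = 336.3, so 337 by the normal approximation. The t-test solution is 337.2, rounded up to 338. Power at 338 per group: 0.25 × √(338/2) = 0.25 × 13 = 3.25; 3.25 − 1.96 = 1.29; power 90.1%. The plan's figure reproduces, for an unadjusted comparison of two means.

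**Step 2: what the covariate model estimates.** With equal SDs, the within-arm slope of the 12-month score on the 6-month score is r. The treatment coefficient is therefore

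adjusted effect = d12 − r × d6, with residual SD = √(1 − r²).

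Power follows from (adjusted effect / residual SD) × 13 − 1.96. For d6 = 0.25 and r = 0.5: 0.25 − 0.125 = 0.125; 0.125 / 0.866 = 0.144; 0.144 × 13 = 1.88; power 47%.

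**Step 3: results with d12 = 0.25 SD and 338 per group.**

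| d6 (SD) | r | Adjusted effect (SD) | Share of d12 removed | Power |
|---|---|---|---|---|
| 0.25 | 0.3 | 0.175 | 30% | 66% |
| 0.25 | 0.5 | 0.125 | 50% | 47% |
| 0.25 | 0.7 | 0.075 | 70% | 28% |
| 0.125 | 0.3 | 0.2125 | 15% | 82.5% |
| 0.125 | 0.5 | 0.1875 | 25% | 80% |
| 0.125 | 0.7 | 0.1625 | 35% | 84% |
| 0 | 0.3 | 0.25 | none | 93% |
| 0 | 0.5 | 0.25 | none | 96% |
| 0 | 0.7 | 0.25 | none | 99.5% |

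**Step 4: simulation check.** With 200,000 simulated infants and a true effect of 0.25 SD at both ages, the covariate model gave 0.126 (r = 0.5) and 0.077 (r = 0.7), against 0.253 unadjusted in both runs. In complete simulated data for 4,000 infants, a GEE with both scores as outcomes and a treatment-by-visit term returned exactly the raw 12-month difference: 0.199 and 0.199 at r = 0.5, 0.248 and 0.248 at r = 0.7. The attenuation comes from conditioning on the 6-month score, not from using GEE.

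**The case against.** The case for leaving the plan largely alone has four parts.

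- **The t-test is intact.** The paragraph on the primary outcome opens with an unadjusted 12-month t-test, and the sample size matches that test. The Abstract names the t-test and a multiple linear regression, with no 6-month covariate. This stands. A reader might infer that the trial's 12-month effect would be lost or reported as null; the text does not support that, because the t-test keeps the total effect and the planned 90% power.
- **Not all of the 6-month benefit is removed.** This also stands. The amount removed is r × d6, which equals the whole 6-month effect only if the slope is 1.
- **A harmless reading exists.** The stated reason for GEE fits a repeated-measures model, and the article plans GEE in that way for weight, length and head circumference. This stands in part. The covariate reading is favoured by the verb but not settled, so a definite bias cannot be claimed. The words still do not describe a repeated-measures model and need correcting even if one was meant.
- **The size rests on assumptions.** True: r and d6 are not in the article, and with no 6-month effect the covariate would raise power.

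It might also be said that a condensed article leaves such detail to the full plan. But this is a stated choice of covariate for the primary outcome, not an omission.

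**Conclusion.** The point holds for the adjusted 12-month analysis only. The sentence specifies an outcome on the treatment pathway as an adjustment variable and, in the same breath, a method that needs that variable on the other side of the model.

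Under the covariate reading, the consequence runs from a gain in power (no 6-month effect) to a fall to between 66% and 28% (6-month effect equal to the 12-month effect, r from 0.3 to 0.7). These figures assume equal SDs, 338 infants per group and a true 12-month effect of 0.25 SD. Under the repeated-measures reading there is no attenuation.

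The practical risk is two 12-month estimates that answer different questions, with no stated order of precedence between them.

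**What to change.** Reword the sentence in Statistical analyses in one of two ways:

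1. Remove the 6-month DASII score from the covariates of the adjusted 12-month regression; or
2. Fit a GEE or mixed model with the 6- and 12-month scores both as outcomes and with visit, treatment, treatment-by-visit and baseline covariates, and report its 12-month treatment contrast as the adjusted estimate.

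Either is enough. The adjusted estimate should stand beside the planned t-test; the longitudinal contrast need not replace it as the primary comparison. State which of the two takes precedence if they differ. Any model conditional on the 6-month score should be labelled exploratory and described as the difference at 12 months given the 6-month score. If option 2 is chosen, note that birth weight, in the plan's covariate list, is also measured after randomisation and so is not a baseline covariate.

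The cost is a change of wording and a few lines of Stata code. No new data are needed. The Blinding section keeps the analysis team blinded until the last infant turns 1 year, and the article reports 15% of enrolled mothers as having completed, so at that stage the change could be made before unblinding.

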#### Secondary outcome(s)

Difference in proportions of infants with developmental delay between the DHA and placebo group at 12 months. Developmental delay will be defined as a DASII score ≤ 70.Mean difference in infant size (weight, length and head circumference) and APGAR score at birth.Mean change in infant size (weight, length and head circumference) at birth, 1 month, 6 months and 12 months between the DHA and placebo group.Mean difference in number of still births, preterm and low birth weight babies between DHA and placebo groups.Difference in infant morbidity patterns (types of illness, frequency and duration of specific conditions) between DHA and placebo group.

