Secondary outcomes:Birth outcomes – Data are collected by a research assistant from hospital records within 24 h after delivery. In case of night deliveries, records from hospital staff are obtained the next morning. All hospital staff were apprised of the variables being collected, procedures and data collection methods before the start of the trial. A periodic (every 6 months) refresher training has also been provided to the staff. The data include whether the birth was a live birth, sex of baby, type of delivery, and anthropometric measurements. Birth weight is measured to the nearest 10 g by using a digital pediatric scale. Low birth weight is defined as recorded birth weight less than 2500 g. Birth length and head circumference are measured by trained hospital staff to the nearest 1 mm using a portable anthropometer with a fixed headpiece and a flexible tape, respectively, according to standard procedures. Gestational age at birth in days is determined based on the dating ultrasound. Preterm delivery is defined as delivery after 20 weeks and before 37 weeks of completed gestation. Foetal losses during pregnancy – including miscarriages/abortions and still-births are recorded by study personnel on site or details are brought by field workers (in case mother went to any other hospital). Stillbirths are defined as fetuses delivered at 20 weeks of gestation or later with no signs of life and recorded as occurring before or during the onset of labor; neonatal deaths are defined as deaths among live-born infants occurring within 28 days after delivery.Infant weight, length and head circumference at 6 and 12 months are measured during their scheduled PKH visits. Questions about infant’s health are asked by the field-staff during home-visits (postpartum). Copies of the health-reports from the child’s paediatrician (whether at PKH or elsewhere) are collected. After the screening procedure, at the time of recruitment, data for contact information, maternal obstetric medical history, demographic details and socio-economic status also have been collected by the trained research assistant using pre-tested questionnaires. Anthropometric measurements of both mother and father have been recorded. Dietary intakes of fatty acids were evaluated using a previously validated food-frequency questionnaire adapted for use in pregnant women (recall period- past 3 months) also have been recorded.Fatty acid profile: Fatty acid composition of RBC membrane phospholipids are appropriate biomarkers of fatty acid status and reflects dietary intakes. Linoleic acid (18:2n-6); Alpha-linolenic acid (18:3n-3); Arachidonic acid (20:4n-6); Eicosapentanoic Acid (20:5n-3); DHA (22:6n-3) will be measured for this study. Lipids will be extracted form the RBC membrane, phospholipid fraction will be separated by thin layer chromatography (TLC), esterified by procedure described by Lepage and Roy [49] and subjected to gas chromatography (GC) for separation and identification. Non fasting maternal blood samples (5 ml) were obtained by veni-puncture at recruitment, delivery and 6 months postpartum. Neonatal blood samples were obtained from the umbilical cord vein immediately after delivery using the syringe method [50]. A 2 ml venous blood sample was obtained 12 months of age from infants. All samples were collected into tubes containing disodium ethylene diamine tetraacetic acid (EDTA). Plasma and RBCs were separated by cold centrifugation at 800 g for 10 min. Plasma was aliquoted and stored at − 80 °C for later analysis.Breast-milk polyunsaturated fatty acids (PUFAs): Breast-milk samples (1 day, 1 month and 6 months postpartum) are taken from 30% random sub-sample. The milk-samples are from a morning feed but not the first one, between 8 and 12 o’clock at PKH. Infants are allowed to suckle the nipple for a few minutes, and then a breast-milk sample (10 ml) is expressed (manual, by mothers themselves) and the feeding continued [51]. The samples are refrigerated immediately (to prevent bacterial growth) and later aliquoted into smaller containers, filled nearly to the top to minimize oxidation, and frozen at − 80 °C until analysis. Before storage, butylated hydroxytoluene is added to a final concentration of 75 μg/mL to prevent lipid oxidation. Since breast-milk PUFA will be expressed as a percent of total fatty acids, complete breast expressions are not required. The samples will be analysed by gas chromatography using standard methods [52].

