For longitudinal analysis of weight, length and head circumference (i.e. at birth, 1 month, 6 month and 12 month), we will also compare the average growth trajectories of the infants between the treatment and placebo groups using Generalized Estimating Equation (GEE) models. The adjusted analyses will also be performed adjusting for time, maternal weight and height, breast-feeding practices and maternal dietary intake.

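### The adjusted infant growth model conditions on breast-feeding practices, which follow both randomisation and birth, so its DHA effect is not a clean randomised contrast

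*Protocol article*

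**What the plan says.** All references are to the Protocol article.

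- **Outcome.** Secondary outcome(s) lists "Mean change in infant size (weight, length and head circumference) at birth, 1 month, 6 months and 12 months". Study design gives the same four times.
- **Analysis.** Statistical analyses sets a GEE comparison of average growth trajectories by arm, "For longitudinal analysis of weight, length and head circumference (i.e. at birth, 1 month, 6 month and 12 month". It then adds an adjusted analysis, "adjusting for time, maternal weight and height, breast-feeding practices and maternal dietary intake".
- **Treatment period.** Under Exposure, women start capsules at or before 20 weeks of gestation and continue to 6 months after delivery.
- **Breast-feeding.** Table 1 has no row for it, and Data collection does not say when or how it is recorded. The nearest item is the Dietary Intake row, marked at enrolment for the woman and at 6 and 12 months for the child.
- **The 1-month measurement.** Data collection describes size at birth and then says "Infant weight, length and head circumference at 6 and 12 months are measured during their scheduled PKH visits". In Table 1 the block headed "Data obtained on child" has columns for birth, 6 months and 12 months. The row "Anthropometry (weight, length, mid upper arm circumference, head circumference of offspring" is marked in all nine columns. These include 1 month postpartum, but that column stands in the woman's block.

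**The concern.** Covariates fixed before randomisation can be added to a model without changing what the treatment effect means, because randomisation balances them in expectation. Breast-feeding practices are not of that kind. Supplementation starts in pregnancy and can continue through six months of lactation, so feeding can respond to treatment. It can also respond to the baby: an infant who is small at birth may be fed differently. Once feeding is in the model, the DHA coefficient compares infants with the same feeding pattern, and randomisation does not make those infants comparable across arms.

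Birth size shows the problem most clearly. It is one of the four sizes in the model, and no later feeding can have caused it. Adjusting it for feeding can only condition on something downstream of the outcome or of its causes.

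At stake is the reading of the adjusted growth result. If the adjusted and unadjusted estimates differ, the reader cannot tell gained precision from an induced distortion.

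**Working it through.** The plan gives no figure for the growth analysis. Its sample size concerns the DASII score, and this point does not depend on it. The check is one of time order, followed by short algebra.

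**Time order, from the article**

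| Item | When | Relation to randomisation |
|---|---|---|
| Maternal height, weight and diet at enrolment | at or before 20 weeks | baseline |
| Start of DHA or placebo | from randomisation | – |
| Birth size (model outcome) | delivery | after |
| Breast-feeding practices (covariate) | after delivery; recording time not stated | after |
| Size at 1, 6 and 12 months (model outcomes) | after delivery | after |

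Whatever the recording time, breast-feeding comes after randomisation and after birth size. Its order relative to the 1-month size cannot be settled from the article.

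**What adjustment does.** Let A be the arm, Y the size at a given time, B a feeding variable and τ the randomised (total) effect of A on Y. In a linear model with a common slope δ of Y on B within arms,

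adjusted effect = τ − δ × Δ,

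where Δ is the difference between arms in mean B.

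- For a covariate measured before randomisation, Δ is zero in expectation, so the adjusted effect still estimates τ.
- For breast-feeding, Δ need not be zero. Take birth size and suppose B = cY + dA + e, so that feeding responds to size (c) and to treatment (d). Then Δ = cτ + d, and the adjusted effect is τ − δ(cτ + d).
- With d = 0, δc equals ρ², the squared within-arm correlation of feeding with birth size. The adjusted effect is then τ(1 − ρ²), which is pulled towards zero.
- With d not zero, the shift can go either way.
- With both τ and d zero, there is no distortion.

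The article gives none of c, d, δ or ρ, so no numerical size follows.

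**The 1-month measurement.** Three places name 1 month as a time for infant size: Study design, Secondary outcome(s) and Statistical analyses. Two places do not list it for the infant: the Data collection text and Table 1's child block. The anthropometry mark at 1 month postpartum does not settle the matter. Its row names the offspring, but the same row is also marked at enrolment and monthly in pregnancy, so marks in the woman's block cannot all be infant measurements.

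**The case against.** The other side has four fair arguments.

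- *The harm is limited.* The adjusted model is additional to an unadjusted GEE, the outcome is secondary, and birth size has its own t-test and regression. All of this stands.
- *Feeding drives infant growth, so adjusting for it is natural.* It may explain variation in later size, but that does not restore the randomised contrast. An effect of DHA not passing through feeding is a mediation question with further assumptions, and the article does not present the model as that.
- *Some contrasts may escape.* Suppose the comparison is a treatment-by-time interaction, feeding enters as one time-constant term, and every infant has all four sizes. The interaction is then untouched and only the overall treatment difference shifts. The article does not fix these conditions.
- *Definition and timing of a covariate belong in the analysis plan.* True, and the missing recording time is not the point. The article itself names breast-feeding as a covariate, and no recording time could place it before birth size.

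Two stronger readings are tempting, and the article supports neither.

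- A reader might infer that feeding is first recorded at 6 months, after both the birth and the 1-month sizes. That rests on the child Dietary Intake row, which is a different item. Feeding in the first month could also precede the 1-month size.
- A reader might infer that infants are not measured at 1 month, or only in the breast-milk sub-sample. The anthropometry row is marked at 1 month postpartum without the 30% limit that the milk row carries. Data collection does not say that 6 and 12 months are the only later times, and women have fortnightly contacts. What remains is an unreconciled schedule.

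**Conclusion.** The point holds for the adjusted growth model. It conditions on a variable that arises after randomisation and after birth, during a period when treatment may still be running, so its DHA coefficient is not a clean randomised contrast. For birth size, one of the four outcomes in the model, this is certain from time order alone.

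The extent is unknown. Distortion requires that mean feeding differs between arms, through treatment or through an effect of treatment on size, and that feeding is associated with size within arms. Both are plausible, but the article quantifies neither. The unadjusted GEE and the primary DASII comparison are untouched by this point. It merits a correction to a secondary analysis and does not threaten the trial's main result.

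The 1-month schedule is a minor clarification. It shows no loss of data and gives no reason to drop that time from the outcome.

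**What to change.** 1. Remove breast-feeding practices from the adjusted growth model. Keep time, and restrict the other covariates to those measured before randomisation: maternal weight, height and dietary intake at enrolment. The enrolment time should be stated for weight, because Table 1 also marks the woman's anthropometry at later visits.
2. Report breast-feeding practices by arm as a separate description. If the role of feeding in any DHA effect is of interest, add a mediation analysis that is labelled exploratory and states its assumptions and when feeding was recorded.
3. Make the Data collection text and Table 1's child block agree with Study design, Secondary outcome(s) and Statistical analyses on whether infants are measured at 1 month, and for whom.

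The cost is a change of wording, with no new visit or measurement. Whatever precision feeding might have added at the later ages is given up. The change can still be made blind: under Blinding, analysts are unblinded only after the last infant reaches 1 year, and the CONSORT statement section reports that about 15% of mothers had completed the trial.

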### Missing data

**S**ensitivity analyses will be performed using complete case analysis and multiple imputation for missing data to evaluate the potential effect of missing outcomes.

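### The growth analysis uses GEE with no stated weighting and keeps multiple imputation for sensitivity; a repeated-measures mixed model, or GEE on imputed or weighted data, needs a weaker missing-data assumption at almost no cost (minor)

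*Protocol article*

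**What the plan says.** The protocol article's *Secondary outcome(s)* list includes change in infant weight, length and head circumference over birth, 1, 6 and 12 months. For these, *Statistical analyses* states that "we will also compare the average growth trajectories of the infants between the treatment and placebo groups using Generalized Estimating Equation (GEE) models", with adjusted versions to follow. It gives no weighting, no working correlation and no analysis scale (kg and cm, or standardised scores).

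On loss, *Effect size, power and sample size* says that "a final sample of 338 infants per group (676 mother-child dyads) was required at the end of the study". It reports 957 mothers recruited, "allowing for potential attrition due to serious adverse events, withdrawal, and migration out of the study area". It states no attrition percentage. *Statistical analyses* adds: "Comparisons on baseline characteristics will also be made between the final study sample and those who were lost to follow up". *Missing data* plans sensitivity analyses by "complete case analysis and multiple imputation for missing data to evaluate the potential effect of missing outcomes". The main growth result is therefore the GEE fitted to whatever sizes were observed.

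**The concern.** GEE without weights is in general guaranteed consistent only when the chance of remaining in follow-up does not depend on the outcomes, given the covariates in the model. There is an exception. For a continuous outcome, a GEE whose working covariance is close to the truth behaves almost like a likelihood model, and then copes with loss that depends on sizes already observed.

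Two choices the protocol leaves open could break that exception. One is an independence working structure. The other is analysis on the raw scale with one common variance, if variance rises with age.

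If small or faltering infants then left more often in one arm than in the other, the 12-month comparison would be shifted. A difference could appear where there is none, or a real one could be masked. A likelihood-based model on the same data needs only that loss depend on observed sizes.

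**Working it through.** **Step 1: the plan's own figure.** Inputs from *Effect size, power and sample size*: 0.25 SD, two-sided α = 0.05, 90% power. n per group = 2(z₀.₉₇₅ + z₀.₉₀)²/d² = 2(1.960 + 1.282)²/0.25² ≈ 336.2, so 337. The t-test version gives 337.2, so 338. Power at 338 per group is 90.1%. The stated 338 per group (676 in total) reproduces.

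**Step 2: room for loss.** 957 - 676 = 281, and 281/957 = 29.4%. This is an implied ceiling counted from recruited mothers, not a forecast of infants lost after birth.

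**Step 3: why the working covariance matters.** In effect, the model predicts a lost infant's 12-month size from earlier sizes. The true slope on one earlier size is ρ × SD₁₂/SD_earlier. A common-variance exchangeable GEE uses ρ alone. The documents give no SDs. With assumed weight SDs of 0.42, 0.52, 0.85 and 1.0 kg, the ratio is 1.0/0.85 = 1.18 from 6 months and 1.0/0.52 = 1.92 from 1 month, so the GEE corrects too little. Independence GEE makes no such correction. With equal SDs the ratio is 1 and most of the problem goes.

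**Step 4: size, by simulation.** Assumptions: no true effect, 957 infants, the SDs above, correlations 0.40 to 0.85, and loss depending on the last observed weight (log-odds per SD, as shown). Ranges cover repeated runs. Entries are the absolute bias at 12 months and the rejection rate at nominal 5%.

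| Dependence of loss on size | Loss | Exchangeable GEE | Independence GEE | Unstructured likelihood model |
|---|---|---|---|---|
| 0.35, one arm only | 29% | 0.040 kg, 8–10% | 0.08 kg, 16% | ≤0.004 kg, 4–7% |
| 0.5, one arm only | 29% | 0.054–0.059 kg, 13–15% | 0.10–0.11 kg, 27–30% | ≤0.004 kg, 4–7% |
| 0.7, one arm only | 29% | 0.075–0.078 kg, 16–17% | 0.14–0.15 kg, 45–46% | ≤0.004 kg, 4–7% |
| 0.5 v 0.25 | 29% | 0.02–0.03 kg, 6–7% | not run | not run |
| 0.5, one arm only | 15% | 0.02–0.03 kg, 5–7% | not run | not run |
| 0.35 v 0.175 | 15% | 0.008 kg, 5% | not run | not run |
| Equal in both arms | 29% | ≤0.01 kg | ≤0.01 kg | ≤0.01 kg |

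With 500 replicates, the Monte Carlo standard error of a 5% rate is √(0.05 × 0.95/500) = 1.0 percentage point, so 4–7% is compatible with 5%.

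Rough check: the GEE standard error was about 0.071 kg when loss was unrelated to size. A bias of 0.054 kg is 0.054/0.071 = 0.76 SE, which gives rejection of Φ(-1.20) + Φ(-2.72) ≈ 12%. A bias of 0.10 kg is 1.41 SE, which gives about 29%. Both are close to the simulated rates.

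**Step 5: where variances are equal or nearly so.** At log-odds 0.5 in one arm and 29% loss, exchangeable bias was 0.013 to 0.016 SD on standardised sizes. It was 0.027 SD (6.7% rejection) when the SD rose by a ratio of 1.25. With assumed flatter SDs for length and head circumference it was about 0.03 and 0.02 SD; independence GEE stayed near 0.10 SD for both.

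**Step 6: loss that depends on the unseen size.** With log-odds 1 per SD in one arm and equal SDs, exchangeable GEE and the likelihood model were both biased by 0.09 to 0.11 SD, with rejection of 26–31%.

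**Step 7: efficiency.** With loss unrelated to size, the standard error was 0.069 kg for the likelihood model against 0.071 kg for GEE.

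**The case against.** The case for leaving the plan alone is substantial. GEE is a standard method for growth data, and the outcome is secondary. Working correlation, weighting and scale are details an article may leave to the full protocol or analysis plan, so their absence is no fault. Multiple imputation is already planned, so part of the question is only which analysis is called the main one. All of that stands, and it is why the point is minor.

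Several stronger readings are tempting, and the documents do not support them:

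- A reader might infer that GEE is unbiased only if loss is unrelated to size. That is too strong: with a working covariance near the truth, the bias from loss tied to observed size is small (Step 5).
- A reader might infer that selective loss alone creates a false DHA effect. With no true effect, it must differ between arms. In a double-blind placebo-controlled trial nothing shows that it does, although nothing excludes it.
- A reader might take 29.4% as loss from the growth data. The adverse events in Table 3 include abortion, intrauterine death and stillbirth. Those pregnancies have no growth trajectory, and withdrawal or migration before delivery leaves none either.
- A reader might assume analysis in kg and cm. The protocol names the measures, not the scale.
- A reader might think that a mixed model removes the problem. It does so only for loss that depends on observed sizes (Step 6).

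What survives is that the protocol itself fixes the model class, and places the remedy for missing outcomes only among the sensitivity analyses.

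**Conclusion.** The point holds as a minor, inexpensive improvement to a secondary analysis. It is not an error that invalidates the growth result. Under one-arm-only dependence (log-odds 0.5 per SD, 29% loss, the assumed weight SDs), the 12-month bias is about 0.05 kg with exchangeable GEE (about 14% rejection) and 0.10 kg with independence GEE (about 27%), against about 0 with an unstructured mixed model. For exchangeable GEE, milder arm differences or 15% loss reduce it to about 0.02 to 0.03 kg and at most about 7% rejection. Where variances are equal or nearly so it is about 0.01 to 0.03 SD, and with equal dependence in both arms it is negligible.

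The SDs, correlations and dropout slopes are all assumptions, because the documents give none. The recommendation does not rest on any one scenario: the likelihood model needs a weaker missing-data assumption, and where the methods were compared its standard error was equal or slightly smaller.

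**What to change.** In the longitudinal growth paragraph of *Statistical analyses*, make the main analysis a linear mixed model for repeated measures on all available sizes. Use visit as a category, an unstructured covariance with its own variance at each visit, and treatment-by-visit contrasts. If GEE is preferred, run it on multiply imputed data, or with inverse-probability-of-remaining weights, as the main growth analysis.

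Keep the planned sensitivity analyses, since neither model protects against loss that depends on unseen size.

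The cost is the wording of one paragraph, with the same data and software. *Blinding* places analyst unblinding after the last infant turns 1 year, so the change should be fixed before then. The downside is reliance on a correctly specified mean and covariance. Four visits and over 600 infants support an unstructured form.
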